## Final Protocol and Statistical Analysis Plan

### 12. Brief Study Description

This is a single-center, parallel-group, non-inferiority, randomized, controlled trial. The investigators from Peking Union Medical College Hospital (PUMCH), Beijing, China, hypothesize that withholding hydrocortisone replacement therapy during the perioperative period in patients with pituitary adenomas (PAs) whose hypothalamus pituitary adrenal (HPA) axis function are intact are safe as compared with the conventional hydrocortisone replacement therapy.

This trial was approved by the Institutional Review Board at Peking Union Medical College Hospital (PUMCH, no. ZS-2608), and was registered with the *clinicaltrials.gov* database (no. NCT04621565).

### 13. Study Design

Study Type: Interventional (Clinical Trial)

Estimated Enrollment: 436 participants

Allocation: Randomized

Intervention Model: Parallel Assignment

Intervention Model Description: Participants are assigned to one of two groups, in a 1:1 ratio, to use hydrocortisone or not to use it during peri-operation of pituitary surgery.

Masking: Triple (Participant, Investigator, Outcomes Assessor)

Masking Description: Participants, investigators, and outcome assessors are all prevented from having knowledge of the interventions assigned to individual participants. Care providers (nurse and resident) know the individualized interventions.

### 14. Background Description

PAs account for approximately 17% of primary brain histologies and 90% of sellar lesions in adults, with an annual incidence of 4.36 per 100000 population in the United States. Apart from hypersecretion symptoms, e.g. Cushing's syndrome and acromegaly, PAs can cause hypopituitarism by compressing the surrounding pituitary gland and thus increasing the pressure of sella. Hypopituitarism can also be a surgical consequence due to the mechanical and vascular injury to the pituitary gland during adenomectomy.

Adrenal insufficiency (AI) or the life-threatening adrenal crisis, presenting as dysfunction of the HPA axis, is one of the most lethal subtypes of hypopituitarism, leading to lethargy, fever, vomiting, tachycardia, low blood pressure, circulatory failure, and even death. Since two cases were reported in the 1950s who died of acute postoperative AI because of withdrawal of glucocorticoids, stress-dose glucocorticoid replacement therapy has been recommended as the standard of care during perioperation of major surgeries, especially for the patients receiving continuous steroids replacement therapy.

Perioperative glucocorticoid supplementation has long been a routine practice for patients with PAs. There is consensus that patients with insufficient baseline HPA-axis function or low serum cortisol levels after surgery for Cushing's disease need steroids supplementation. However, according to the recent non-randomized studies, for those with an intact preoperative HPA-axis, which accounts for the majority of patients with PAs, withholding perioperative steroids replacement therapy might be safe and not lead to a higher risk of postoperative AI and could avoid steroids-related adverse events.

Two recent randomized trials suggested that perioperative steroids would be safely withheld under intensive monitoring of postoperative serum cortisol in patients with an intact HPA axis.

However, because of the observative nature of non-randomized studies and the exceedingly small sample sizes (43 and 40 cases) that were not sufficient to calculate the incidence of postoperative AI and the improper types of glucocorticoid used (dexamethasone and prednisone) in the two clinical trials, a well-designed randomized trial with adequate sample size using the physiological type of steroids (hydrocortisone) is warranted to address this long-lasting but unsolved clinical concern.

We aim to conduct this randomized trial to investigate whether the new protocol of withholding perioperative hydrocortisone supplementation is non-inferior to hydrocortisone replacement therapy in terms of the incidence of acute AI during perioperation in patients with an intact HPA-axis scheduled for pituitary adenomectomy. We hypothesize that the new treatment protocol is non-inferior to the conventional regimen, with an ultimate goal to minimize unnecessary steroid overuse. In addition, we evaluated the incidence of AI in the 3rd postoperative month, the prognostic factors for events, the incidences of adverse events during 3 months after surgery, and the pattern of postoperative HPA axis function changes without hydrocortisone supplementation.

## 15. Arms and Interventions

### Arm 1:

**Experimental:** No-hydrocortisone group (Patients receive no perioperative hydrocortisone)

**Intervention/treatment:** No hydrocortisone or other steroids are given before, during, and after the surgery. These patients are given 100 ml of normal saline intravenously instead of hydrocortisone sodium succinate, which needs to be dissolved in 100 ml of normal saline in hydrocortisone group, followed by placebo tablets with a similar appearance to the hydrocortisone tablets. If a patient develops postoperative AI, he/she needs to receive hydrocortisone treatment (hydrocortisone sodium succinate, 100mg, iv., every 12 hours [q12h] for 2 days, and subsequent hydrocortisone tablets, 20mg, po., bid for 1 month). After these treatments, patient symptoms and serum cortisol levels are evaluated every week. The taper program should be started in patients with a normal morning serum cortisol level.

## **Arm 2:**

**Active Comparator:** Hydrocortisone group (Patients receive perioperative hydrocortisone)

**Intervention/treatment:** Hydrocortisone sodium succinate dissolved in 100 ml of normal saline (0.9%) is given intravenously (iv.) on the day of operation (OD, 100 mg at 8 am and 100 mg at 8 pm), POD1 (100 mg at 8 am and 50 mg at 8 pm), and POD2 (25 mg at 8 am). Hydrocortisone tablets were subsequently given per mouth (po.) from the afternoon of POD2 (20 mg, twice a day [bid] for a week, and 20 mg once a day [qd] for another week) and were stopped at the start of the third postoperative week. If a patient develops postoperative AI, he/she needs to stop his/her original protocol and receive the modified hydrocortisone treatment regimen (hydrocortisone sodium succinate, 100mg, iv., every 12 hours [q12h] for 2 days, and subsequent hydrocortisone tablets, 20mg, po., bid for 1 month). After these treatments, patient symptoms and serum cortisol levels are evaluated every week. The taper program should be started in patients with a normal morning serum cortisol level.

## **16. Outcome Measures**

### **1) Primary outcome**

- Incidence of newly-onset **acute AI [During the perioperative period]**

*Adrenal insufficiency:* Lower-than-normal morning serum cortisol level ( $< 5 \mu\text{g/dl}$ ) at 8 a.m., plus at least one of the AI-related symptoms.

*The perioperative period:* This period as defined in this trial includes the preoperative period in the ward, the day of operation, and the 1st and 2nd day after surgery.

## 2) Secondary outcome

- Incidence of newly-onset **late AI** [From POD3 to the 3rd postoperative month]

*Adrenal insufficiency:* Lower-than-normal morning serum cortisol level ( $< 5 \mu\text{g/dl}$ ) at 8 a.m., plus at least one of the AI-related symptoms.

## 3) Other Outcome Measures:

- Rate of newly-developed **diabetes mellitus** [During the first 3 postoperative months]

*Diabetes mellitus:* A fasting plasma glucose level  $\geq 126 \text{ mg/dl}$  ( $7.0 \text{ mmol/l}$ ) or the 2-h plasma glucose value  $\geq 200 \text{ mg/dL}$  ( $11.1 \text{ mmol/L}$ ) after the oral glucose tolerance test.

- Rate of newly-developed **diabetes insipidus** [During the first 3 postoperative months]

*Diabetes insipidus:* Urine volume  $> 300 \text{ ml/h}$  for more than 3 consecutive hours, urine specific gravity  $< 1.005$ , and serum sodium  $> 145 \text{ mmol/l}$ .

- Rate of **electrolyte disturbance** [During the first 3 postoperative month]

*Electrolyte disturbance* is defined as lower-than- or higher-than-normal levels of serum sodium ( $135\text{-}145 \text{ mmol/l}$ ), potassium ( $3.5\text{-}5.5 \text{ mmol/l}$ ), and calcium ( $2.13\text{-}2.70 \text{ mmol/l}$ ).

- Rate of **deep venous thrombosis** [During the first 3 postoperative months]

*Deep venous thrombosis* is detected by the ultrasound.

- Rate of **decreased bone density** [During the first 3 postoperative months]

*Decreased bone density* is detected by the dual-energy x-ray absorptiometry.

## 17. Inclusion and Exclusion Criteria

### Inclusion Criteria:

- Patients with PAs that need transsphenoidal surgery, whose HPA axis are intact
- Patients of either gender aged from 18 years to 70 years

### Exclusion Criteria:

- Patients with Cushing's disease
- Patients with PAs who have AI before surgery
- Patients with pituitary apoplexy or other acute pituitary conditions that need emergency surgery
- The postoperative pathology result indicates that the tumor is not a PA
- Patients that refuse to participate or those who ask to quit after enrollment
- Patients who needed continuous glucocorticoid replacement therapy due to other diseases
- Patients who were pregnant

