## 18. Sample Size Estimation

- We design the study as a non-inferiority trial to address the clinical question of whether the no-hydrocortisone protocol is non-inferior to the traditional regimen regarding the incidences of new-onset acute AI during perioperation after surgery for PAs in patients with an intact HPA-axis.
- The sample size is calculated based on the between-group comparison of the primary outcome (the incidences of new-onset AI during perioperation) to detect a 10% difference on the incidence of AI (as indicated by the 95% CI) during perioperation of pituitary surgery. The non-inferiority margin ( $\delta$ ) is thus set as 0.1.
- The calculation formula for qualitative data in non-inferiority trials ( $N=2 \times [U\alpha + U\beta]^2 \times P[1-P]/\delta^2$ ) is used, with  $\alpha$  set at 0.05 and  $\beta$  at 0.2.
- According to the published literature (DOI: 10.3171/2019.11.JNS192381; DOI: 10.1093/neuros/nyy479) and our preliminary observation, we set  $\sigma$  as 0.2.
- Assuming a 10% loss to follow-up, the sample size is finally determined as 218 in each trial group and 436 in total.

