## 20. Statistical Analysis Plan

- This is a single-center, parallel-group, non-inferiority, randomized, controlled trial.
- We follow the CONSORT guideline for reporting the result of this trial.
- Qualitative data are to be presented as numbers, percentages, and 95% CI, and quantitative data are to be presented as means and standard deviations.
- Analyses of the primary, secondary, and other outcomes will be performed by calculating the 95% CI of the difference: mean incidence (no-hydrocortisone group) – mean incidence (hydrocortisone group).
- Non-inferiority is identified if the upper limit of the 95% CI is smaller than the margin of 10 percent points.
- We assess superiority for the outcomes in which the non-inferiority is achieved.
- Post hoc subgroup analyses and prognostic analyses will be performed for the primary and secondary outcomes.
- We use the receiver operator characteristic (ROC) curve to detect the cut-off value of baseline serum cortisol in predicting early and late postoperative AI.
- The student's t-test will be used for comparisons of continuous variables and chi-squared test for categorical variables.
- A P value < 0.05 is considered statistically significant.

691     **21. Randomization sequence**

| VAR00001 | Random | Group | VAR00001 | Random | Group | VAR00001 | Random | Group |
|----------|--------|-------|----------|--------|-------|----------|--------|-------|
| 1        | 0.87   | 2     | 31       | 0.54   | 2     | 61       | 0.26   | 1     |
| 2        | 0.34   | 1     | 32       | 0.58   | 2     | 62       | 0.91   | 2     |
| 3        | 0.60   | 2     | 33       | 0.96   | 2     | 63       | 0.20   | 1     |
| 4        | 0.04   | 1     | 34       | 0.21   | 1     | 64       | 0.23   | 1     |
| 5        | 0.56   | 2     | 35       | 0.41   | 1     | 65       | 0.34   | 1     |
| 6        | 0.91   | 2     | 36       | 0.74   | 2     | 66       | 0.08   | 1     |
| 7        | 0.94   | 2     | 37       | 0.76   | 2     | 67       | 0.41   | 1     |
| 8        | 0.85   | 2     | 38       | 0.53   | 2     | 68       | 0.57   | 2     |
| 9        | 0.47   | 2     | 39       | 0.99   | 2     | 69       | 0.46   | 1     |
| 10       | 0.71   | 2     | 40       | 0.32   | 1     | 70       | 0.30   | 1     |
| 11       | 0.57   | 2     | 41       | 0.30   | 1     | 71       | 0.60   | 2     |
| 12       | 0.55   | 2     | 42       | 0.34   | 1     | 72       | 0.13   | 1     |

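### Quitting after enrollment is listed as an exclusion with no time limit and no analysis set is named, so randomised patients can be removed for a reason that may depend on outcome

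*Supplement*

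**What the plan says.** The exclusion list in Section 17 of the final protocol contains two items that can be known only after a patient has entered the trial. One covers "Patients that refuse to participate or those who ask to quit after enrollment". The other reads "The postoperative pathology result indicates that the tumor is not a PA". Neither has a time limit or says what happens to data already collected.

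Section 20 describes the design: "This is a single-center, parallel-group, non-inferiority, randomized, controlled trial". It gives the method, "Analyses of the primary, secondary, and other outcomes will be performed by calculating the 95% CI of the difference", and the decision rule, "Non-inferiority is identified if the upper limit of the 95% CI is smaller than the margin of 10 percent points". The rest covers superiority, subgroups, an ROC analysis, the tests and the significance level. The readable text does not define an all-randomised (intention-to-treat) or a per-protocol set, a missing-outcome rule or a sensitivity analysis. The CONSORT statement in Section 20 concerns reporting. Section 18 allows for 10% loss to follow-up but does not say how lost patients are analysed.

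Section 16 defines the primary event as a low 8 a.m. cortisol plus at least one AI-related symptom, with a window that ends on the second day after surgery. Late AI, the secondary outcome, runs from day 3 to month 3.

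**The concern.** Quitting after enrollment cannot be an eligibility criterion. Placed in the exclusion list of a plan with no analysis set, it works as permission to remove randomised patients. It has no time limit, so a patient who quits in week 6 falls under it even though the primary outcome was complete on day 2. An observed primary outcome could then be discarded although nothing is missing.

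Patients who feel ill are plausible quitters, and a symptom is part of the event. If AI cases leave the analysis more often than other patients, both arms' rates fall, and the higher rate falls by more percentage points. If they leave mainly from the no-hydrocortisone arm, the difference shrinks faster. Either way the estimate moves towards the result the trial hopes to show, and non-inferiority can be declared when the true difference is at the margin.

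**Working it through.** **The plan's own figure.** Section 18 gives N = 2(Uα + Uβ)² P(1 − P)/δ², with α 0.05, β 0.2, δ 0.1, and 0.2 for a quantity written σ, which I read as P. One-sided α gives 2 × (1.645 + 0.842)² × 0.2 × 0.8 / 0.01 = 197.8, so 198 per arm, and 198 × 1.1 = 218. The stated 218 is reproduced and used below.

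**Set-up.** The true difference is placed exactly at the margin. Non-inferiority is declared if the upper Wald limit is below 0.10:

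p₁ − p₀ + 1.96 × √[p₁(1 − p₁)/n₁ + p₀(1 − p₀)/n₀] < 0.10

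(1 = no hydrocortisone, 0 = hydrocortisone). The interval is taken as two-sided.

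**Effect of removing quitters.** If a share f of AI cases in an arm with true rate p quit and are excluded, and no non-cases quit, then

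- expected number removed = 218 × p × f
- remaining n = 218 × (1 − pf)
- apparent rate = p(1 − f)/(1 − pf)

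Example: p = 0.30 and f = 0.20 remove 218 × 0.30 × 0.20 = 13.1 patients, leave about 205, and give an apparent rate of 0.24/0.94 = 25.5%.

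The documents give no quit rates, so f is an assumption. The last column is an exact sum over both binomial distributions with n rounded.

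| True rates | AI cases who quit | Removed (no-HC / HC) | Apparent rates | Apparent difference, points | False non-inferiority |
|---|---|---|---|---|---|
| 30% v 20% | none | 0 / 0 | 30.0% v 20.0% | 10.0 | 2.5% |
| 30% v 20% | 10%, both arms | 6.5 / 4.4 | 27.8% v 18.4% | 9.5 | 3.4% |
| 30% v 20% | 20%, both arms | 13.1 / 8.7 | 25.5% v 16.7% | 8.9 | 4.9% |
| 30% v 20% | 10%, no-HC only | 6.5 / 0 | 27.8% v 20.0% | 7.8 | 7.8% |
| 30% v 20% | 20%, no-HC only | 13.1 / 0 | 25.5% v 20.0% | 5.5 | 19.8% |
| 15% v 5% | none | 0 / 0 | 15.0% v 5.0% | 10.0 | 3.1% |
| 15% v 5% | 10%, both arms | 3.3 / 1.1 | 13.7% v 4.5% | 9.2 | 5.5% |
| 15% v 5% | 20%, both arms | 6.5 / 2.2 | 12.4% v 4.0% | 8.3 | 10.5% |

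At 15% v 5% the starting point is 3.1% because the Wald limit is slightly liberal at low rates. Simulation with a random number of quitters agrees with the exact figures to within about 0.2 percentage points.

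**When non-cases quit too (30% v 20%).** If 10% of cases and 5% of non-cases quit in both arms, the figure is 2.9%. If the same happens in the no-hydrocortisone arm only, it is about 4.6% to 4.7%. If 10% quit at random in both arms, it stays at about 2.5%.

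**One illustrative data set.** All randomised: 55/218 v 44/218 is 25.2% v 20.2%, a difference of 5.0 points with standard error 4.0, so the upper limit is 12.9 and non-inferiority is not met. If 8 of the 55 cases quit and are excluded: 47/210 v 44/218 is 22.4% v 20.2%, a difference of 2.2 points with standard error 3.96, so the upper limit is 9.95 and non-inferiority is met. Eight patients are 3.7% of one arm, inside the 10% loss that Section 18 allows for.

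**The case against.** The strongest reply has four parts.

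- **No passage says that outcomes recorded before withdrawal are thrown away.** Section 17 is an eligibility list and Section 20 is silent. The patient-flow figure, which might name the analysed set, was not available to this review. This stands in part: the omission is certain for the readable text only, and a reader should not infer that the sponsor has committed to discarding recorded outcomes. But the only written rule on quitters is that they are excluded, and nothing in Section 20 counters it.
- **Differential quitting is limited by design.** Participants, investigators and assessors are masked (Sections 13 and 19), with saline and look-alike tablets, and both arms receive the same treatment if AI develops (Section 15). The primary window closes on day 2. This stands, and makes the one-arm rows of the table less likely for the primary outcome. It does not remove the problem: nurses and residents know the allocation, equal quitting among AI cases still raises the error, and the exclusion outlasts the window. Late AI, followed to month 3, has less of this protection.
- **Pathology is different.** Tumour type is fixed before randomisation and cannot be caused by the assigned arm. This stands. A reader might group the two exclusions as equally biasing, and the documents do not support that.
- **A request to quit may be withdrawal of consent.** It cannot simply be relabelled as stopping study drug, because further data collection may not be permitted. This stands, and shapes the fix.

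**Conclusion.** The point holds in a limited form. Section 17 contains a rule that can remove randomised patients at any time for a reason that may be related to outcome, and Section 20 has no analysis set to prevent it. That much rests on the text.

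The size rests on assumed quit rates. At the margin with 218 per arm, equal quitting of 10% to 20% of AI cases raises false non-inferiority to 3.4% to 4.9% (30% v 20%) or 5.5% to 10.5% (15% v 5%). Quitting confined to the no-hydrocortisone arm raises it to about 8% to 20% (30% v 20%). All of these assume that only AI cases quit; where other patients quit too, the effect is smaller, and random quitting has almost none.

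A reader might infer that symptomatic patients will leave one arm and produce a false claim, with error rates of 40% or more. Such figures arise only if 30% or more of AI cases quit from the no-hydrocortisone arm alone. The documents give no quit rates to support that, and the masking and short primary window argue against it. The supported statement is that the plan allows this bias, not that it will occur.

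**What to change.** 1. **Section 17:** delete the part of the exclusion that concerns quitting after enrollment, and handle it as withdrawal, recording the date, the reason and whether consent for further data collection is withdrawn.
2. **Section 20:** state that the primary analysis includes every randomised patient in the assigned arm, using all outcome data collected up to withdrawal of consent. Apply the same rule to late AI.
3. **Section 20:** add a per-protocol analysis as a supporting check.
4. **Section 20:** add one missing-outcome sensitivity analysis, for example counting missing as AI in the no-hydrocortisone arm and as no AI in the hydrocortisone arm, or a tipping-point analysis.
5. **Non-PA pathology (a lesser issue):** decide any such exclusion blind to arm, and show the result with and without these patients.

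The cost is wording in two sections and a few extra table columns, with no new patients or visits. The downside is slight dilution of the difference from patients who went off protocol, which the per-protocol analysis makes visible.

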## Patients Flow

[figure not shown]

## 18. Sample Size Estimation

- We design the study as a non-inferiority trial to address the clinical question of whether the no-hydrocortisone protocol is non-inferior to the traditional regimen regarding the incidences of new-onset acute AI during perioperation after surgery for PAs in patients with an intact HPA-axis.
- The sample size is calculated based on the between-group comparison of the primary outcome (the incidences of new-onset AI during perioperation) to detect a 10% difference on the incidence of AI (as indicated by the 95% CI) during perioperation of pituitary surgery. The non-inferiority margin ( $\delta$ ) is thus set as 0.1.
- The calculation formula for qualitative data in non-inferiority trials ( $N=2 \times [U\alpha + U\beta]^2 \times P[1-P]/\delta^2$ ) is used, with  $\alpha$  set at 0.05 and  $\beta$  at 0.2.
- According to the published literature (DOI: 10.3171/2019.11.JNS192381; DOI: 10.1093/neuros/nyy479) and our preliminary observation, we set  $\sigma$  as 0.2.
- Assuming a 10% loss to follow-up, the sample size is finally determined as 218 in each trial group and 436 in total.

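### The sample size is built on a one-sided 5% alpha but non-inferiority is judged on a 95% CI, so power at the planned event rate is about 70%, not 80%

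*Supplement*

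**What the plan says.** Section 18 (Sample Size Estimation) of the final protocol in the Supplement sets up a non-inferiority comparison of two proportions using N = 2(Uα + Uβ)²P(1 − P)/δ². The inputs are:

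- Error rates: the formula "is used, with $\alpha$ set at 0.05 and $\beta$ at 0.2". Whether α is one-sided or two-sided is not stated.
- Margin: "The non-inferiority margin ( $\delta$ ) is thus set as 0.1".
- Event-rate input: citing two published trials "and our preliminary observation, we set $\sigma$ as 0.2". The formula has no σ; its only such term is P.
- Result: "Assuming a 10% loss to follow-up, the sample size is finally determined as 218 in each trial group and 436 in total".

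The same section links the calculation to the confidence interval, describing it as intended "to detect a 10% difference on the incidence of AI (as indicated by the 95% CI").

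Section 20 (Statistical Analysis Plan) gives the decision rule: "Non-inferiority is identified if the upper limit of the 95% CI is smaller than the margin of 10 percent points". The difference is no-hydrocortisone minus hydrocortisone. Neither section mentions a 90% CI or a one-sided 95% bound.

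**The concern.** The α in a non-inferiority sample size has to match the error rate of the interval used for the decision. The upper limit of an ordinary 95% CI leaves 2.5% in the tail, so the matching quantile is 1.96. The published number appears to come from 1.645. If so, β = 0.2 describes a test that the trial will not run.

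What is at stake is the meaning of the stated power. If the upper limit landed above 10 points, readers would take the failure as coming from a trial with 80% power at its planning assumptions, when its chance of success under those assumptions was clearly lower.

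**Working it through.** **Inputs.** From Section 18: δ = 0.1, β = 0.2 (Uβ = 0.8416), α = 0.05, 10% loss, 218 per arm. P = 0.2 is the reading of the figure labelled σ. A single P implies equal incidence in both arms and a true difference of 0. From Section 20: success if the upper 95% limit is below 0.10.

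**Step 1: reproduce the plan's figure.** With Uα = 1.6449 (one-sided 5%):

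N = 2 × (1.6449 + 0.8416)² × 0.2 × 0.8 / 0.1² = 197.8, so 198 per arm.

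198 × 1.1 = 217.8, so 218 per arm. This matches exactly.

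**Step 2: try the other readings.**

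| Reading | N per arm before loss | Gives 218 after 10% loss? |
|---|---|---|
| P = 0.2, Uα = 1.645 | 198 | Yes (× 1.1) |
| P = 0.2, Uα = 1.96 | 252 (from 251.2) | No: 278 (× 1.1) or 280 (/ 0.9) |
| 0.2 as an SD | 50 (1.645) or 63 (1.96) | No |
| 0.2 as a variance | 248 (from 247.3; 1.645) or 314 (1.96) | No |

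Of these, only P = 0.2 with a one-sided 5% α yields the published number.

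**Step 3: power under the rule in Section 20.** With a two-sided 95% CI,

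power = Φ(δ / √(2P(1 − P)/n) − 1.96) = Φ(0.1 / √(0.32/n) − 1.96).

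| Evaluable per arm | 0.1/√(0.32/n) | Power, 95% CI rule | Power, one-sided 5% rule |
|---|---|---|---|
| 196 (218 less 10%) | 2.475 | 69.7% | 79.7% |
| 198 (the calculated N) | 2.487 | 70.1% | 80.0% |
| 218 (no loss) | 2.610 | 74.2% | 83.3% |

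A simulation of the Wald interval with one million trials at each size gave 69.8%, 70.5% and 74.4% for the 95% CI rule, so the normal approximation is not responsible for the shortfall.

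**Step 4: size needed for 80% under the written rule.** 252 evaluable per arm; 252/0.9 = 280 randomised per arm, 560 in total.

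**Step 5: dependence on the event rate.** With 196 evaluable per arm and the 95% CI rule, power is 91% at a common rate of 10%, 79% at 15%, 70% at 20%, 63% at 25% and 58% at 30%. To reach 80%, P(1 − P) may be at most 196 × 0.01 / [2 × (1.96 + 0.8416)²] = 0.1249, that is, P of about 14.6% or lower.

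**Step 6: loss allowance.** A 10% loss from 218 leaves 218 × 0.9 = 196.2, so 196, short of the 198 calculated. Dividing by 0.9 gives 220 per arm. This matters little: 196 against 198 is about 0.4 points of power.

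**The case against.** The arithmetic is not in dispute. The case on the other side concerns interpretation and weight.

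- **Sidedness is inferred.** Section 18 says only that α is 0.05, and Section 20 never says two-sided. If a one-sided 95% bound was meant, the two sections agree and power is about 80%. This is a fair caveat, but nothing in the text supports that reading. Section 20 uses the same 95% CI wording for descriptive percentages, and goes on to test superiority where non-inferiority is met, with P < 0.05 as the threshold. Even if a one-sided bound was intended, it would have to be written down.
- **The error is in the safe direction.** This stands. The 95% CI rule is the stricter one, type I error is not inflated, and a positive non-inferiority result is not weakened.
- **The 70% is conditional.** It assumes a 20% rate in both arms and 10% lost from the primary analysis. The primary window closes on the second postoperative day (Section 16), so loss to follow-up bears mainly on the month-3 outcome. With all 218 evaluable, power would be 83% at a 15% rate. This also stands, but Section 17 still removes patients for non-adenoma pathology and withdrawal. The 20% rate and the 10% loss are the plan's own figures, and at 20% even full retention gives only 74%.
- **The labelling and loss-inflation slips are minor.** Agreed. They are worth correcting only because the same paragraph has to be rewritten.

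**Conclusion.** The concern holds. Section 18 reproduces 218 per arm only with a one-sided 5% α, while Section 20 decides on a 95% CI. Under the plan's own assumptions (20% incidence in both arms, no true difference, 10% loss) the type II error is about 0.30 rather than 0.20. Power is 69.7% at 196 evaluable per arm and 74.2% with no loss, so at that incidence no level of retention delivers the stated β.

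The conclusion rests on three readings: that σ = 0.2 means P = 0.2, that α was applied one-sided (both inferred from the exact match to 218), and that the 95% CI is the usual two-sided one. A true incidence of about 14.6% or lower would restore 80% power with 196 per arm; a higher incidence than planned would lower power further. The power statement for the primary outcome is wrong as written and must be corrected. The validity of a positive result is not affected.

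**What to change.** Keep 436 patients and the 95% CI decision rule, and restate Section 18 as follows:

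- Give α as one-sided 0.025, matching the upper limit of a two-sided 95% CI, and say in Section 20 that the interval is two-sided.
- Replace σ = 0.2 with P = 0.2, and state that it is the assumed incidence in both arms with a true difference of 0.
- State 218 randomised and about 196 evaluable per arm, with power of about 70% at P = 0.2 (74% with no loss).
- Add power by common event rate at 196 per arm: about 91% at 10%, 79% at 15%, 70% at 20% and 63% at 25%.
- Write the loss allowance as n/(1 − 0.10).

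Two other changes would also make the sections agree: enlarging the trial to 280 per arm, or declaring a one-sided 5% rule. The first means 124 more patients (560 − 436). The second relaxes the success criterion, which is hard to defend when the summary of changes shows that some outcome incidences had already been re-evaluated for the article. Restating the power avoids both. It costs a rewording of Section 18, a short clarification in Section 20, and a less favourable power figure. No extra patients are needed, and the margin and decision rule stay the same.
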